**Methods:**

This research uses a quantitative approach divided into 2 distinct phases. In phase 1, we conduct a descriptive survey to assess the level of awareness and use of mobile apps for iADLs and identify the factors that influence the use of such apps among older adults. To ensure clarity and comprehension among participants, we provide them with a subject information sheet in both Kannada and English. The data collected during this phase enable us to gain insights into awareness levels, use patterns, and factors that shape older adults’ use of apps for iADLs. The results serve as the foundation for designing the GEP. In phase 2, a cluster randomization method will be used to select older adults aged 60 to 75 years in Udupi district, Karnataka, India, who are active smartphone users. These participants will be divided into 2 groups: the experimental and the control groups. The experimental group will join the GEP. The sample size for phase 1 is 554, and phase 2 is 50. To assess the effectiveness of this program, we will measure the outcomes before and after its implementation using the same assessment tools used in phase 1.

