### Sample Size

Sample size calculations were performed separately for phase 1 and phase 2 of the study. For phase 1, a sample size of 369 participants was estimated based on proportion values. This sample size was then adjusted by a design effect of 1.5 to account for potential clustering or stratification, resulting in a required sample size of 554 participants. In phase 2, the focus was on comparing 2 proportions. To ensure the study’s robustness in the face of potential dropouts (estimated at 20%), an initial sample size of 31 participants was calculated for each group. This initial size was adjusted by a design effect of 1.5 to consider the study’s specific design characteristics, yielding a total required sample size of 46 participants per group, rounded up to 50 participants per group.

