### Statistical Analysis

#### Plan for Data Analysis

To evaluate the awareness and use of mobile apps among older adults, frequency and percentage distribution will be used as a statistical method. A combination of statistical techniques will be used to analyze the influencing factors, including descriptive statistics to provide a summary of the data and logistic regression to model the relationship between the influencing factors and mobile app use. A sequence of statistical tests will be applied to measure the effectiveness of the GEP. These tests include repeated measures ANOVA, 2-tailed *t* test, Mann-Whitney *U* test, Wilcoxon signed rank test, and *χ*^2^ test. These tests will help assess the impact and changes brought about by the GEP on various outcome measures.

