### Conclusions

Following the successful testing of the GEP, there will be an opportunity to recommend its implementation to welfare departments. This proposal encourages older adults to embrace mobile apps for performing iADLs. Additionally, establishing a mobile app training initiative can provide training and support to older adults in using these apps effectively.

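### Phase 2 is sized on two proportions of an unnamed outcome, and no primary outcome or deciding between-arm test is designated to which that size can be tied

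*Protocol article*

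**What the plan says.** Protocol article, Sample Size: "In phase 2, the focus was on comparing 2 proportions". The outcome behind the proportions, their values, the significance level and the power are not given. The figures that are given are "potential dropouts (estimated at 20%), an initial sample size of 31 participants was calculated for each group", a design effect of 1.5, and a result of "yielding a total required sample size of 46 participants per group, rounded up to 50 participants per group".

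Plan for Data Analysis: a sequence of tests is to measure effectiveness. "These tests include repeated measures ANOVA, 2-tailed *t* test, Mann-Whitney *U* test, Wilcoxon signed rank test, and *χ*^2^ test". Their target is left open: "These tests will help assess the impact and changes brought about by the GEP on various outcome measures".

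The nearest thing to a primary outcome is the primary objective under Principal Findings, which joins two constructs, awareness and use. Research Instrument says both are measured across 8 iADL components. The Conclusions look ahead to use of the result: "Following the successful testing of the GEP, there will be an opportunity to recommend its implementation to welfare departments". The article does not say what would count as success.

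**The concern.** A sample size has meaning only for a stated outcome and a stated test. Here the size is set for a binary comparison, while the analysis paragraph offers one test for proportions and four for scores or ranks, with none marked as deciding. A reader of the final report could not tell which result the trial was sized for.

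With several overlapping tests and at least two constructs, the choice of the result to emphasise could be made after the data are seen. One listed test, the Wilcoxon signed rank test, is a paired test. Applied before and after within the trained group, it does not compare that group with control. What is at stake is whether a statement that the programme works, passed on to welfare departments, rests on a pre-specified randomised comparison.

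**Working it through.** **1. The plan's own figure.** 31 × 1.5 = 46.5 per group. The article gives 46; strict rounding up gives 47; 50 covers both. The starting 31 cannot be rebuilt, because no proportions, significance level or power are stated.

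**2. What 31 would imply for two proportions.** Assumptions (not in the article): two-sided 5%, 80% power, control rate 10% to 50%. The wording suggests that the 20% dropout is already inside the 31, so evaluable n = 31 × 0.8 = 24.8, about 25 per group. Formula:

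n = [1.96·√(2p̄(1−p̄)) + 0.8416·√(p₁(1−p₁) + p₂(1−p₂))]² / (p₂−p₁)²

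For 10% vs 44.5%: p̄ = 0.2725, and n = (1.234 + 0.489)² / 0.345² ≈ 25. Likewise 30% vs about 69% and 50% vs about 86%. The implied difference is about 35 to 39 points. If 31 were the figure before dropout, it would be about 30 to 35 points, and 47 / 0.8 = 58.75, so 59 per group would be needed. Nothing in the article says which of these was meant, or for which outcome.

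**3. What 50 per group would detect on a score.** Evaluable n = 50 × 0.8 = 40. Effective n = 40 / 1.5 = 26.7 per group. With the same 5% and 80%, in a normal approximation:

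SMD = (1.960 + 0.8416) × √(2 / 26.67) = 2.8016 × 0.2739 = 0.77

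At 90% power it is 0.89. Power is 45% for SMD 0.5 and 83% for SMD 0.8. With baseline adjustment at an assumed correlation of 0.5, the detectable SMD is 0.77 × √0.75 = 0.66. The number of organisations is not given, so these figures do not allow for having few clusters.

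The abstract says "The sample size for phase 1 is 554, and phase 2 is 50", without a per-group qualifier, and this must be reconciled with Sample Size. If 50 were the total, effective n would be 25 × 0.8 / 1.5 = 13.3 per group and the detectable SMD 2.8016 × √(2 / 13.33) = 1.09.

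**4. False-positive chance if every listed test is run.** This was simulated with no programme effect and no before-after change: 5,000 trials, 40 evaluable per arm, no clustering, baseline to post-test correlation 0.5. For two outcomes, the post-test components not explained by baseline were correlated at 0.5. Between-arm tests were the t test, Mann-Whitney, a t test on change (equivalent to the group-by-time term of a repeated measures ANOVA with two time points), and chi-square on the score cut at its centre. The Wilcoxon signed rank test was then added within one arm. The table gives the chance of at least one p<0.05:

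| Outcomes | Between-arm tests only | With within-arm Wilcoxon |
|---|---|---|
| One | 12.3% | 15.6% |
| Two (awareness, use) | 23.0% | 28.1% |

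The tests overlap, so one outcome stays below the figure for five independent tests, 1 − 0.95⁵ = 22.6%. For comparison, one test on each of two independent outcomes gives 1 − 0.95² = 9.8%.

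**5. What the simulation leaves out.** It assumes no drift over time. If both arms improved between measurements, the within-arm Wilcoxon test would tend to be significant with no difference between arms. It also ignores clusters. The size carries a design effect of 1.5, but none of the five tests as named accounts for the organisations.

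**The case against.** The strongest reply is that the article is consistent with itself. Chi-square is the natural test of two proportions and it is listed, and the same paragraph describes awareness and use by frequencies and percentages. The t test and Mann-Whitney test are usual alternatives chosen by data type, so the list may be a menu and not five tests of everything. Test order and multiplicity rules commonly sit in an analysis plan, which is not shown.

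Much of this stands, and it rules out three stronger readings.

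- A reader might infer that the size is wrong for the analysis, or that the trial is underpowered. Neither is shown: a matching test is present, and no target difference is stated against which power could fall short.
- A reader might count awareness and use over 8 components as 16 endpoints and quote 1 − 0.95¹⁶ = 56%. The article describes questionnaire content and plans no component-level tests, so that figure has no basis in it.
- A reader might take the Conclusions sentence as a decision rule under which any significant result suffices. It is a discussion remark. No success rule or significance level is given, so the inflation above is conditional.

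The reply does not supply the missing link. Which outcome the trial is sized for, and which between-arm comparison decides it, belongs with the stated sample-size basis. The article gives a basis and a list of tests and leaves them unconnected.

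**Conclusion.** The point holds in a limited form. Phase 2 is sized on two proportions of an unnamed outcome, and the analysis designates no primary outcome or test, so the stated size cannot be tied to a deciding analysis.

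The false-positive chance exceeds 5% only if all listed tests are run and any unadjusted p<0.05 is taken as success. It is then about 12–16% for one outcome and 23–28% for awareness and use together, in a simulation without clustering and under the correlations stated. The detectable SMD of about 0.77 describes what 50 per group offers and is not evidence of a shortfall. It assumes two-sided 5%, 80% power, 20% loss and a design effect of 1.5. The article places phase 2 in the months ahead, so the gap can still be closed before outcome data exist.

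**What to change.** Before phase 2 starts:

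1. Name one primary outcome, at the sponsor's choice: the binary awareness or use outcome behind the two-proportion calculation, or a total use score.
2. Name one primary between-arm analysis of it at post-test, adjusted for its baseline value and accounting for organisation as the cluster.
3. Tie Sample Size to that outcome. If binary, state the two proportions, the significance level and the power. If a score, state what 50 per group detects (SMD about 0.77 unadjusted, on the assumptions above).
4. Place the other construct second in a fixed order. Label the remaining tests, any component-level results and all within-group before-after tests as supportive.
5. State that any conclusion of successful testing rests on the primary result.

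Cost: revised wording in Sample Size and Plan for Data Analysis, and a sentence in Conclusions. Naming the analysis does not itself add participants, but whether 50 per group is enough can be judged only once a target difference is stated. The downside is that secondary, component-level and within-group results can no longer be claimed as proof of effectiveness.

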#### Develop and Determine the Effectiveness of a GEP

The GEP will be a comprehensive intervention designed to facilitate the use of smartphone apps for iADLs. The development of GEP will be based on the findings from the study’s first phase, incorporating insights from experts in health care, mobile technology, and older adults’ welfare departments or organizations. The structure of the GEP program will encompass the following components: information and features—detailed information about smartphone apps relevant to iADLs, including their features and functionalities; installation procedures—step-by-step guidance on installing and setting up these smartphone apps; general awareness—fundamentals of smartphone use and general awareness regarding its capabilities; security awareness—guidelines on ensuring smartphone security and safe use; dos and don’ts—best practices and precautions for effective and responsible smartphone use; operation manuals—manuals provide instructions on operating specific smartphone apps for iADLs. The training program will be conducted through 8 sessions, each lasting 3 hours. These sessions will incorporate hands-on training using audiovisual facilities to enhance participants’ understanding and practical skills in using smartphone apps effectively for iADLs.

## Results

### Overview

This study is funded by the Indian Council of Medical Research (Adhoc/193/2022/SBHSR on November 18, 2022). Phase 1 data collection is expected to be completed by November 2023, and phase 2 is scheduled to commence in the upcoming months. Phase 1 and 2 findings will be analyzed and discussed in the main paper, which we intend to submit to a high-quality peer-reviewed journal for publication. The research protocol, informed consent forms, and associated documentation received approval from institutional ethics committees (214/2020).

### Expected Outcomes

The expected outcomes are as follows: The data collected from this study will provide valuable insights into the actual awareness levels and the influencing factors affecting the use of mobile apps for iADLs among older adults. The design and testing of the GEP have the potential to significantly enhance the ability of older adults to manage iADLs, leading to improved self-management and overall well-being, which in turn has a positive societal impact. To further extend the benefits of this research, collaboration with nongovernmental organizations and self-help groups can be explored to implement the GEP on a larger scale. This would allow for a broader reach and greater empowerment of older adults. Additionally, the results of this study can serve as a valuable reference for other researchers seeking to empower older adults in using mobile technologies. As part of the GEP, developing the iADLs Guide, a mobile app providing regular updates on technology, will be an ongoing service for older adults. This tool will ensure older adults have access to the latest information and updates in the ever-evolving field of mobile technology, further enhancing their ability to perform iADLs effectively. This initiative contributes to achieving sustainable development goal 4.3.2 to provide education to the general public and encourage lifelong learning [25].

## Discussion

### Principal Findings

The primary objective of the GEP is to enhance awareness and use of mobile apps among older adults for iADLs. The study findings can improve older adults’ participation in the GEP, significantly increasing awareness and usage levels. This aligns with previous research, such as the study by Xie and Kalun Or [26], which demonstrated that targeted interventions like mHealth can effectively improve technology adoption and use among older adults. In our research, the GEP provided structured guidance, hands-on training, and resources to bridge the gap in awareness and facilitate the use of mobile apps for iADLs. One of the noteworthy outcomes of the GEP was its positive impact on the QOL among older adults. The program can empower older adults to perform iADLs more independently and efficiently, enhancing well-being. This finding resonates with existing literature. For instance, a study by Sen et al [27] emphasized through a systematic review that using technology, including mobile apps, can reduce social isolation, increase engagement in daily activities, and improve mental and physical well-being among older adults. The GEP’s focus on addressing the specific needs of older adults in iADLs aligns with the principles of person-centered care and empowerment.

The success of the GEP can be attributed to its tailored approach. The program was developed based on older adults’ specific needs and preferences, considering technological anxiety and resistance to change. This personalized approach aligns with the recommendations of Charness and Boot [28], who emphasized the importance of designing technology interventions that consider individual differences and provide ongoing support. The GEP’s combination of information, hands-on training, and ongoing assistance through the iADLs Guide mobile app ensured that older adults received the necessary support at every stage of their technology adoption journey. Collaboration with older adults’ welfare organizations, nongovernmental organizations, and self-help groups is pivotal in successfully implementing the GEP. This collaborative approach resonates with Baker et al [29] findings, highlighting the importance of involving community organizations in technology interventions for older adults. The positive outcomes observed in this study suggest that the GEP model can be scaled up and replicated in other regions and populations, further extending its benefits to a larger demographic of older adults.

This protocol addresses a pressing issue—the growing digital divide among older adults. Older adults may face challenges in keeping pace with technological advancements as the world becomes increasingly digital. This protocol aligns with the findings of the Pew Research Center, which reported that while technology adoption among older adults is rising, a substantial digital divide persists. The GEP represents an effort to bridge this divide and empower older adults to leverage technology for iADLs. This protocol builds on prior research, highlighting the potential benefits of technological interventions for older adults. For example, a systematic review by Wildenbos et al [30] emphasized that technology interventions can enhance older adults’ independence, well-being, and social connectivity. This protocol seeks to contribute to the existing body of knowledge by assessing the effectiveness of a structured empowerment program tailored to older adults’ unique needs and challenges in adopting mobile apps for iADLs.

The study plan and methodology emphasize on assessing the real-world impact of the GEP. While many studies have explored the potential benefits of technology for older adults in controlled settings, this protocol seeks to evaluate the program’s effectiveness in the context of participants’ daily lives. This aligns with the recommendations of Mitzner et al [31], who stressed the importance of studying technology use in ecologically valid environments to capture its true impact. Therefore, this protocol for the effectiveness of GEP represents a significant endeavor to empower older adults with the necessary skills and knowledge to use mobile apps for iADLs. Drawing from supportive studies and available evidence, the protocol underscores the importance of addressing the digital divide, tailoring interventions to individual needs, and collaborating with stakeholders to enhance the well-being and independence of older adults in the digital age.

### Limitations

Acknowledging the study protocol’s limitations and ethical considerations is crucial. The sample size may be restricted to a specific geographic area, and participants will need a baseline level of English literacy. Researchers must ensure informed consent and safeguard participants’ privacy and data security, following established ethical guidelines.

### Conclusions

Following the successful testing of the GEP, there will be an opportunity to recommend its implementation to welfare departments. This proposal encourages older adults to embrace mobile apps for performing iADLs. Additionally, establishing a mobile app training initiative can provide training and support to older adults in using these apps effectively.

## Abbreviations

ADL: activity of daily living
GEP: gerontechnology empowerment program
iADL: instrumental activity of daily living
ICT: information and communication technology
mHealth: mobile health
QOL: quality of life
